## Statistical analysis

8

### Thresholds for statistical and clinical significance

8.1

We will assess if the thresholds for statistical significance and clinical significance are crossed using the five-step procedure as suggested by Jakobsen and colleagues [14]. This procedure will include adjustments of thresholds for significance according to the number of outcome comparisons and the number of randomised participants in relation to the planned sample size [14]. Accordingly, we will analyse all continuous outcomes using Trial Sequential Analysis to take into account the early stopping of the trial [14,27]. When analysing the results using Trial Sequential Analysis, we will use the minimal important differences and the SDs defined in the paragraph above (see ‘Sample size and power considerations’), an acceptable risk of type I error of 1%, and an acceptable risk of type II error of 20% [1,14]. We will use a Bayes factor threshold for significance of 0.1 based on the a priory anticipated intervention effect [14].

### Analysis of quality of life and patient satisfaction

8.2

Primary analysis: linear regression adjusted for the baseline value and the three stratification variables age >65 years (yes/no), insulin treatment at trial entry (yes/no), and treatment at Steno Diabetes Center (yes/no) [1].

Secondary analysis: linear regression adjusted for the baseline value and the stratification variables (see above) and the design variables (sex (male/female), prior cardiovascular disease (yes/no), statin treatment at entry (yes/no), and glutamic acid decarboxylase antibodies (positive/negative)) [1]. We will in a supplementary analysis adjust for metformin administration before trial entry (yes/no).

All analyses will primarily include the modified intention-to-treat population. We will also perform the analyses adjusted for the stratification variables including the per-protocol population [1].

### Analysis of the cardiovascular outcomes

8.3

*Primary analysis:* Cox regression analysis adjusted for the three stratification variables (age >65 years (yes/no), insulin treatment at trial entry (yes/no), and treatment at Steno Diabetes Center (yes/no)) [1].

*Secondary analysis:* Cox regression analysis adjusted for stratification variables (see paragraph above) and other design variables (sex (male/female), prior cardiovascular disease (yes/no), statin treatment at entry (yes/no), and glutamic acid decarboxylase antibodies (positive/negative)) [1]. We will in a supplementary analysis adjust for metformin administration before trial entry (yes/no).

### Assessments of underlying statistical assumptions

8.4

We plan to systematically assess if the assumptions underlying each of the used statistical methods are fulfilled [28].

For all analyses, we will test for major interactions between each covariate and the intervention variable (test of interaction). In turn, we will include each possible first order interaction between included covariates and the intervention variable. For each combination, we will test if the interaction term is significant and assess the effect size. We will only consider that there is evidence of an interaction if the interaction is statistically significant after Bonferroni adjusted thresholds (0.05 divided by number of possible interactions) and if the interaction shows a clinically significant effect. If it is concluded that the interaction is significant, we will consider both presenting an analysis separately for each (e.g. for each site if there is significant interaction between the trial intervention and ‘site’) and an overall analysis including the interaction term in the model.

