**Fig. 1 fig1:**
[figure not shown]
**–** A study scheme of the factorial designed trial, where participants are ranodmised into both factors. Thus, each participant is allocated in both Factor 1 and Factor 2, and receives a combination of the two treatment schemes.

The protocol was approved by the Regional Committee on Biomedical Research Ethics (H-D-2007-112) and the Danish Medicines Agency (EudraCT: 2007-006665-33 CIMT), registered within ClinicalTrials.gov (NCT00657943), and conducted in accordance with The Declaration of Helsinki and guidelines for Good Clinical Practice. Informed consent was obtained from each participant enrolled in the trial.

The design of the CIMT trial and the influence of metformin and insulin on the primary outcomes have previously been reported [2,3]. Here we report the detailed statistical analysis plans for evaluating the effects of these intervention on the patient-centred outcomes quality of life, patient satisfaction, and cardiovascular outcomes.

We plan on reporting the results of these outcomes in two separate papers: one comparing metformin versus placebo comparison and one comparing the three insulin analogue regiments.

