## Deviations from the initial design and methods of the CIMT trial

11

Based on our sample size estimation for the primary outcome of the CIMT trial allowing for five comparisons of the involved intervention groups we planned to include 950 patients [1]. However, eventually only 412 participants were included, as the trial had to be stopped at the scheduled duration of the trial due to lack of financial support. In the present analysis plan we schedule to analyse these clinical outcomes based on a strict factorial 2 × 3 design comparing the effects of metformin versus placebo and comparing the three different insulin analogue regimens. Given the low power in relation to the clinical outcomes, we consider all outcomes to be exploratory and that most emphasis should be given to the quality of life and patient satisfaction results according to our result of the power calculations.

In the original protocol it was not specified how the patient-important quality of life data and clinical outcomes would be analysed and presented [1]. Given the fact that the trial is a 2 × 3 factorial design and two sets of data are presented, we anticipate publishing the data in two separate papers.

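### The 2 × 3 factorial plan leaves the other randomised factor out of its covariate lists and does not prespecify the metformin-by-insulin interaction

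*Protocol article*

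**What the plan says.** Section 11 commits to a "strict factorial 2 × 3 design comparing the effects of metformin versus placebo and comparing the three different insulin analogue regimens". The legend of Fig. 1 confirms that "each participant is allocated in both Factor 1 and Factor 2, and receives a combination of the two treatment schemes". Section 4 bases power on 412 participants for metformin versus placebo and 274 for each insulin pair, so each factor is pooled over the other.

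The models are set out in Section 8:

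- Questionnaires, primary (8.2): "linear regression adjusted for the baseline value and the three stratification variables".
- Questionnaires, secondary (8.2): "linear regression adjusted for the baseline value and the stratification variables (see above) and the design variables". The design variables are sex, prior cardiovascular disease, statin treatment and glutamic acid decarboxylase antibodies.
- Cardiovascular outcomes, primary (8.3): "Cox regression analysis adjusted for the three stratification variables". The secondary model adds the same four design variables.
- Both outcome types have a supplementary adjustment for metformin use before entry.

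On interactions, Section 8.4 states "we will test for major interactions between each covariate and the intervention variable". It takes the covariates in the model one at a time and applies a Bonferroni threshold of 0.05 divided by the number of interactions.

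**The concern.** None of the listed covariates is a randomised allocation. Insulin treatment at entry and earlier metformin use describe the patient before randomisation. The rule in Section 8.4 pairs covariates with the intervention, so the interaction between the two interventions falls outside it. Sections 8.5 and 8.6 check residuals and proportional hazards only.

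Two things are at stake. The first is precision: if the regimens differ in, say, treatment satisfaction, that variation stays in the residual of the metformin model. The second is interpretation: if metformin acts differently with different regimens, the plan reports one average, and no planned analysis would show the difference. Two separate papers are planned, and neither is committed to showing the six cells. The article's stated purpose is to prevent data-driven analysis, so an interaction examined later would be unplanned.

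**Working it through.** **Inputs.** SF-36: relevant difference 4 points, SD 9.5 (Section 4.1). Alpha 0.001; 206 versus 206 participants for metformin; 274 per insulin pair, taken as 137 versus 137 (Section 4). Assumed here: two-sided tests, equal cells of 412/6 = 68.7, SD 9.5 within every cell, no missing data.

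**1. The plan's own power figures.** A plain two-group noncentral t test gives 83.0% for metformin and 56.3% for an insulin pair, exactly as stated. With SD 9 it gives 88.3% and 63.7%, again as stated for ITSQ and Diab-Medsat. The stated figures are therefore pooled two-group tests with no term for the other factor. The normal approximation, used in step 2, gives 83.7% and 57.7% for SF-36.

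**2. Precision lost by leaving the other factor out.** Power = Φ(4 / (SD·√(2/n)) − 3.29).

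- Metformin model, one regimen differing by 4 points from the other two: added variance = 16 × (1/3) × (2/3) = 3.56, which is 3.9% of 9.5² = 90.25. SD becomes √93.81 = 9.69. Power falls from Φ(4.27 − 3.29) = 83.7% to Φ(4.19 − 3.29) = 81.6%.
- Insulin model, 4-point metformin effect: added variance = 16 × (1/2) × (1/2) = 4. SD becomes √94.25 = 9.71. Power falls from Φ(3.48 − 3.29) = 57.7% to Φ(3.41 − 3.29) = 54.8%.

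**3. What the average can hide.** If metformin changes SF-36 by +6 points with one regimen and 0 with the other two, the pooled effect is (6 + 0 + 0)/3 = 2.0, below the 4-point threshold. With 4, 0 and 0 it is 1.33. Both are correct averages, but neither describes any single regimen.

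**4. What an interaction analysis could show.** The difference in metformin effect between two regimens has SE = 9.5 × √(4/68.7) = 2.29, so a 95% interval is about ±1.96 × 2.29 = ±4.5 points.

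| True difference between two regimens | Power at 0.05 | Power at 0.01 |
|---|---|---|
| 4 points | 42% | 20% |
| 8 points | 94% | 82% |

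The 0.01 column is 0.05/5, the Section 8.4 threshold if the other factor became a fifth covariate in the primary linear model. The difference detectable with 80% power is 6.4 points at 0.05 and 7.8 at 0.01. The 2-df test, by noncentral F(2, 406), has noncentrality (68.7/2) × Σ(effect − mean)² / 90.25. For effects 4, 0, 0 this is 34.3 × 10.67 / 90.25 = 4.06, giving 42% and 20%. For 6, 0, 0 it is 9.13, giving 77% and 56%.

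**The case against.** The strongest reply is that the pooled contrast is valid as it stands. Randomisation is 1:1 crossed with 1:1:1, so the linear contrast estimates an average effect without bias, with or without interaction. This stands. A reader might infer that the pooled comparisons answer the trial's question only if the two factors are additive. The documents do not support that: the stated question is the effect of metformin added to insulin and of the three regimens, and an average effect answers it. Additivity bears only on how far the average carries over to each regimen.

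It can also be said that Sections 8.2 and 8.3 list adjustment covariates and do not spell out the treatment term either, so a strict factorial analysis might mean that both factors enter. That reading is possible, though Section 8.4 speaks of one intervention variable. Even then, a rule that pairs covariates with the intervention does not cover the interaction between two interventions. Nor can the trial's original protocol fill the gap, since Section 11 says it did not specify these analyses.

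The remaining replies limit the weight of the point. The precision loss is 2 to 3 percentage points of power. The interaction test is weak, and a non-significant result would not establish additivity. For the cardiovascular outcomes even the main effects have stated power of 9% or less, so an interaction analysis there would tell almost nothing. All outcomes are declared exploratory.

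A reader might also infer that the three regimens must pass an overall test before pairwise comparison. That is a preference: Section 8.1 already commits to adjusting thresholds for the number of outcome comparisons.

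**Conclusion.** The gap is real but moderate. The listed covariates omit the other randomised factor, and the interaction rule does not reach metformin by insulin regimen. The linear pooled estimates are unbiased averages, and no stated sample size or power figure is wrong on this account. In the Cox models, omitting the other factor can slightly attenuate the hazard ratio.

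The precision loss, about 2 points of power for metformin and 3 for an insulin pair, is small even when the other factor has a full 4-point effect. The larger consequence is that no planned analysis shows whether the average holds across regimens. An interval of about ±4.5 points is wide against a 4-point threshold, but it would still be informative about large differences.

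These figures rest on the assumptions listed with the inputs. Exclusions from the modified intention-to-treat population or missing questionnaires would widen the interval. Baseline adjustment would narrow it by an amount the article does not allow one to calculate. The point should be fixed, but it is not a condition for the validity of the planned comparisons.

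**What to change.** - In the modified intention-to-treat population, state that every linear and Cox model contains both metformin (1 df) and insulin regimen (2 df) alongside the covariates already listed.
- For the questionnaire outcomes, prespecify the 2-df metformin-by-insulin interaction. Report its estimates with confidence intervals, and give the six cell summaries in both papers.
- Label the interaction exploratory and do not judge it on a p-value. The pooled contrasts stay the main comparisons.

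The cost is wording and a small extra analysis. With the interaction, the metformin model gains 2 + 2 = 4 degrees of freedom and the insulin model 1 + 2 = 3, with about 412 participants. The planned comparisons and stated power figures are unchanged.

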### Assessments of underlying statistical assumptions for linear regression

8.5

We will visually inspect quantile-quantile plots of the residuals [28,29] to assess if the residuals are normally distributed and use residuals plotted against covariates and fitted values [28,29] to assess for homogeneity of variances. If the plots do not show a straight line, we will consider transforming the outcome, e.g. using log transformation or square root and/or use robust standard errors [28,29].

### Assessments of underlying statistical assumptions for cox regression

8.6

We will visually inspect log-log plots stratified by treatment and adjusted for the effects of all covariates (continuous and categorical) to asses if the assumption of proportional hazards between the compared intervention groups is fulfilled [[28], [29], [30]]. If the assumption of proportional hazards seems violated, we will consider stratifying the regression analysis for the variable not fulfilling the assumption or using a non-parametric test (e.g. log rank test) as the primary analysis method or split the observation period into two (or more) separate observation periods.

## Statistical reports

9

Blinded data on all outcomes will be analysed by two independent investigators [28]. Two independent statistical reports will be sent to the CIMT Steering Committee, and if there are discrepancies between the two primary statistical reports, then possible reasons for that will be identified and it will be considered which is the most correct result [28]. A final statistical report will be prepared, and all three statistical reports will be published as supplementary material.

## Characteristics of patients at baseline

10

We will present a description of baseline characteristics by intervention group. Discrete variables will be summarised by frequencies and percentages. Percentages will be calculated according to the number of patients with available data. Where values are missing, the actual denominator will be stated. Continuous variables will be summarised using standard measures of central tendency and dispersion using either mean ± SD for data with normal distribution or median and interquartile range for non-normally distributed data.

## Deviations from the initial design and methods of the CIMT trial

11

Based on our sample size estimation for the primary outcome of the CIMT trial allowing for five comparisons of the involved intervention groups we planned to include 950 patients [1]. However, eventually only 412 participants were included, as the trial had to be stopped at the scheduled duration of the trial due to lack of financial support. In the present analysis plan we schedule to analyse these clinical outcomes based on a strict factorial 2 × 3 design comparing the effects of metformin versus placebo and comparing the three different insulin analogue regimens. Given the low power in relation to the clinical outcomes, we consider all outcomes to be exploratory and that most emphasis should be given to the quality of life and patient satisfaction results according to our result of the power calculations.

In the original protocol it was not specified how the patient-important quality of life data and clinical outcomes would be analysed and presented [1]. Given the fact that the trial is a 2 × 3 factorial design and two sets of data are presented, we anticipate publishing the data in two separate papers.

## Discussion

12

To avoid risks of outcome reporting bias and data-driven biased results, this paper presents the detailed statistical analysis plan for the CIMT trial analysing patient-relevant outcomes at a time when the data have been gathered but not yet inspected or analysed. This statistical analysis plan follows the guidelines provided by Gamble et al. [31]. Clinical trials ought to be analysed according to a pre-specified analysis plan in order to prevent reporting bias and data driven analysis results [[32], [33], [34], [35]]. We have an obligation to report these patient-centred outcomes of quality of life, patient satisfaction, and cardiovascular outcomes and make the results available for future systematic reviews.

## Strengths

13

This statistical analysis plan has a number of strengths. The overall trial methodology has been pre-defined, we take problems with multiplicity and other risks of random errors into account, use validated statistical methods, and we systematically test for the underlying statistical assumptions [1,14,28]. Furthermore, we will analyse data in accordance to the modified intention-to-treat principle and, if necessary, use multiple imputations, and a best-worst/worst-best case scenario to assess the potential impact of the missing data on the results [26]. We will use the five-step procedure proposed by Jakobsen and colleagues to assess whether the thresholds for statistical and clinical significance are crossed [14].

## Limitations

14

The statistical analysis plan also has limitations. First, the primary outcome of the CIMT trial was an non-validated surrogate outcome [1], and the analyses of the patient-centred outcomes described in the present statistical analysis plan should therefore be considered exploratory. Second, the power estimations of the cardiovascular outcomes showed that we do not have sufficient data to confirm or reject realistic intervention effects [15], so the results of the cardiovascular outcome will only be reported in the supplementary material. Third, this statistical analysis plan has been developed long after data accrual was stopped. However, the plan was developed and agreed upon without knowledge of the intervention effects or specific data.

We plan on a subsequent 10-year follow-up study of the cardiovascular outcomes, assessed using similar methodology as described in this statistical analysis plan. This would compensate for the low power regarding the cardiovascular outcomes because of only 18 months follow-up in 412 patients, we plan to prolong the follow-up for the participants after end of the trial. This would raise the power of our analyses of cardiovascular outcomes, but risk confounding by changes to anti-diabetic treatment after stop of the CIMT interventions.

## Conclusions

15

To avoid risks of outcome reporting bias and data-driven biased results, this article presents the detailed statistical analysis plan for the CIMT trial analysing patient-relevant outcomes at a time when the data have been gathered but not yet inspected or analysed.

## Ethics approval and consent to participate

Central ethical approval has been confirmed from the Regional Committee on Biomedical Research Ethics (H-D-2007-112) and the Danish Medicines Agency (EudraCT: 2007-006665-33 CIMT), registered within ClinicalTrials.gov (NCT00657943), and the trial was conducted in accordance with The Declaration of Helsinki and guidelines for Good Clinical Practice. Informed consent was obtained from each participant enrolled in the trial.

## Consent for publication

Not applicable.

## Availability of data and material

All relevant data are available.

## Data Availability

No data was used for the research described in the article.
